### Interim analyses (21b)

There are no planned interim analyses for either efficacy or futility. There may be safety-focused interim looks performed (without formal statistical testing) at the regular DSMB meetings or at unscheduled times per the DSMB’s request.

### Methods for additional analyses (e.g., subgroup analyses) (20b)

#### Mediators and moderators of outcomes

The difference in sustained PrEP adherence and HCV cure with on-site care relative to referral with patient navigation will be moderated by healthcare system and venue. As part of sensitivity analyses planned for all outcomes, we will examine differences in effects (moderation) with respect to the biological variable, sex, race/ethnicity, and various social determinants of health (e.g., housing instability, food insecurity, employment, income). We will document differences in risk profiles by these same characteristics (sex, race/ethnicity) as well as site and venue. All subgroups will be evaluated with a test of the interaction of the subgroup indicator and the treatment assignment.

### Methods in analysis to handle protocol non-adherence and any statistical methods to handle missing data (20c)

Missing data are a ubiquitous problem in substance use research, primarily due to dropping out and refusal. Missing data can lead to biased estimates and reduction of power, affecting the generalizability of the study. We are making every effort to minimize the amount of missing data. In the primary analyses, we will assume that participants who have dropped out are treatment failures (i.e., are not taking PrEP and, if HCV positive, not taking HCV medications). In all cases, missingness patterns will be identified and analyses will be conducted to determine if there is differential non-death attrition by treatment arm, and if missingness is related to any of the covariates. In the case that covariates predict missingness, the data are called “Missing at Random” (MAR) [68]. GEE analyses are only appropriate if data are “Missing Completely at Random,” which means that no covariates predict the occurrence of missing data. Under the MAR assumption, the multiple imputations procedure can be used to fill in the data without artificially compressing the variance associated with the imputed data [69]. Therefore, if observed covariates predict the existence of missing data, multiple imputation will be used in a secondary analysis of the primary outcome to assess the effects of missingness on the reported results. If nonrandom missingness is of concern (Missing not at Random (MNAR)), this problem will be addressed by applying pattern-mixture, propensity score, or related models so that the effect of bias can be assessed in sensitivity analyses.

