## Statistical methods

### Statistical methods for primary and secondary outcomes (20a)

The *primary hypothesis* is that on-site integrated care is superior to off-site referral with patient navigation in achieving higher rates of sustained PrEP adherence and/or HCV cure, measured as the proportion of participants achieving detectable levels of tenofovir in DBS in the first 6 months of follow-up and achieving HCV sustained virologic response 12 weeks post-treatment completion after initiating treatment within the 6 months post-randomization. A sub-hypothesis is that the difference in rates of sustained PrEP adherence and HCV cure with on-site integrated care relative to referral with patient navigation will be moderated by healthcare system and venue; differences between on-site versus referral will be greater in Miami vs. Montreal and in SSP vs. OAT settings. For the *primary hypothesis*, each of our two co-primary outcomes, sustained PrEP adherence and HCV cure, will be tested at an alpha rate of .025 using a Poisson regression analysis with a binary outcome to directly estimate the risk ratio associated with on-site integrated care (rather than the odds ratio estimated by logistic regression). Both co-primary hypothesis tests will be stratified by site and venue, testing for interactions of treatment effect by site and venue due to our expectation that context is important for implementation. In the absence of qualitative interaction effects, the main effects will be examined.

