We will analyze long-run sustained PrEP adherence and HCV cure resulting from treatment initiated after the first 6 months, similarly, except using a repeated-measures Poisson regression implemented as a generalized estimating equation (GEE) including the periods between 6- and 18-month follow-ups. It is important to note that for all PrEP adherence analyses, any participants who become HIV positive will be counted as PrEP non adherent. For all other secondary outcomes, similar approaches will be used. PrEP initiation will be assessed as a simple binary outcome (initial self-reported use verified by prescription in medical records) and again modeled using repeated measures Poisson regression. We will examine sustained PrEP adherence among those self-reporting taking PrEP to disentangle PrEP non-engagement, inadequate PrEP use, and protective levels of PrEP use. Note that protective levels of PrEP use will be examined only among patients not on HCV medication due to norms for protective PrEP use when taken with HCV medication not having been established. We will examine HCV treatment initiation and rates of SVR among those treated (the primary analysis will include all HCV-positive randomized participants). We will examine potential rates of behavioral disinhibition as measured by changes in self-reported sexual risk (i.e., condom-less vaginal and/or anal sex), needle/works sharing, HCV infection/re-infection rates, and STI (including HIV) infection rates over the entire follow-up period. Additional analyses will examine the timing of initiation of both PrEP and HCV treatment, and whether non-engagement and discontinuation of PrEP are related to levels of (or changes in) risk.

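### Multiple imputation is committed only to the primary outcome, so the repeated-measures GEE secondary analyses, which the plan itself says need completely random missingness, have no stated remedy for covariate-related dropout

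*Protocol article*

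**What the plan says.** Section 20a of the protocol article sets the models. Each co-primary outcome "will be tested at an alpha rate of .025 using a Poisson regression analysis with a binary outcome"; GEE is not mentioned there. The next paragraph brings GEE in for two sets of later results, long-run adherence to PrEP and cure of HCV where treatment started after month 6. These are handled in the same way, "except using a repeated-measures Poisson regression implemented as a generalized estimating equation (GEE) including the periods between 6- and 18-month follow-ups". The same paragraph adds: "For all other secondary outcomes, similar approaches will be used". PrEP initiation is also given a repeated-measures Poisson model. Behavioural disinhibition, HCV infection or re-infection, and STI (including HIV) are to be examined over the entire follow-up.

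Section 20c sets the missing-data rules. In the primary analyses, dropouts are treated as failures, explained as not taking PrEP and, if HCV positive, not taking HCV medication. Missingness patterns are to be examined in all cases. The section then states: "GEE analyses are only appropriate if data are “Missing Completely at Random,” which means that no covariates predict the occurrence of missing data". It describes multiple imputation as suitable under missing at random (MAR) and concludes that, if observed covariates predict missingness, "multiple imputation will be used in a secondary analysis of the primary outcome to assess the effects of missingness on the reported results". A last sentence offers pattern-mixture, propensity score or related models as sensitivity analyses if missing not at random (MNAR) is of concern; it names no outcome.

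**The concern.** The premise of the argument in section 20c is about GEE, but its conclusion reaches only an outcome that section 20a does not analyse by GEE and that the dropout rule has already completed. The analyses to which the premise applies get no stated MAR remedy.

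What is at stake is the secondary evidence to 18 months: durability of adherence, later HCV cure, and the outcomes that would show harm (infection and increased risk behaviour). If people who leave differ from those who stay, an available-case analysis describes those who stay. The trigger is plausible. The COVID-19 impact section reports a 9-month suspension in Montreal that included follow-up assessments, a suspension of over 12 months at the Montreal OAT program, and fewer than 25% of enrolled participants reachable by phone or internet. Site and venue could therefore predict missed visits, which would fail the plan's own definition of missing completely at random.

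**Working it through.** **1. Model against missing-data rule (sections 20a and 20c)**

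| Outcome | Model named | Dropout = failure stated? | Imputation stated? |
|---|---|---|---|
| Co-primary: 6-month PrEP adherence, HCV cure | Poisson regression, binary outcome | Yes | Yes, as a secondary analysis |
| Long-run PrEP adherence, later-initiated HCV cure | Repeated-measures Poisson GEE, 6 to 18 months | Not explicitly | No |
| HCV infection, STI/HIV, risk behaviour | Similar approaches, entire follow-up | No; the rule speaks only of medication | No |

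The MNAR sentence could reach every row, but only if MNAR is a concern and only as a sensitivity analysis.

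**2. The plan's own power figure.** The point does not depend on it, but it reproduces. With 250 per arm, 40% versus 55.5% and two-sided alpha .025 (z = 2.2414): pooled p = 0.4775; null SE = √(2 × 0.4775 × 0.5225/250) = 0.04468; alternative SE = √((0.40 × 0.60 + 0.555 × 0.445)/250) = 0.04414. Power = Φ((0.155 − 2.2414 × 0.04468)/0.04414) = Φ(1.243) = 89.3%, against the stated 90%. Nothing below changes it.

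**3. Illustration for an infection or risk outcome (all inputs assumed).** Half of each arm is high-risk (40% have the outcome) and half low-risk (20%), so the true rate is 30% in both arms. Dropout is 10% among low-risk participants; among high-risk participants it is 30% on-site and 50% off-site.

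- On-site: (0.5 × 0.7 × 0.4 + 0.5 × 0.9 × 0.2)/(0.35 + 0.45) = 0.23/0.80 = 28.75%.
- Off-site: (0.5 × 0.5 × 0.4 + 0.5 × 0.9 × 0.2)/(0.25 + 0.45) = 0.19/0.70 = 27.14%.
- Risk ratio (RR) = 28.75/27.14 = 1.06, where the truth is 1.00.
- Imputation within risk group restores 0.5 × 0.4 + 0.5 × 0.2 = 30% in both arms.

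With 250 per arm, 200 and 175 participants are observed. SE(log RR) = √(0.7125/57.5 + 0.7286/47.5) = 0.167 and log 1.06 = 0.058, so the bias is about 0.35 SE; the 95% interval around 1.06 is about 0.76 to 1.47.

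**4. Illustration for long-run adherence (simulation, all dropout assumed).** 100,000 per arm; visits at 6, 9, 12, 15 and 18 months; true rates 40% off-site and 55.5% on-site at every visit (RR about 1.39); correlation 0.6 between successive visits; dropout depends on adherence at the previous visit. The model is Poisson with arm and visit terms and independence working correlation.

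| Dropout per visit if adherent / not adherent | RR, full data | RR, available-case | RR, dropout = failure | 18-month observed rate, off / on |
|---|---|---|---|---|
| 8% / 8% (completely random) | 1.381 | 1.381 | 1.383 | 39.9% / 55.3% |
| 5% / 12% | 1.388 | 1.372 | 1.403 | 42.7% / 57.9% |
| 5% / 20% | 1.389 | 1.356 | 1.423 | 45.5% / 60.7% |
| 3% / 20% | 1.386 | 1.353 | 1.431 | 46.7% / 61.7% |
| 5% / 12%, off-site × 1.5 | 1.389 | 1.351 | 1.514 | 43.4% / 57.9% |

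When dropout depends on earlier adherence, the available-case RR is 1 to 3% too low (1.372/1.388 = 0.988; 1.351/1.389 = 0.973). The 18-month rates are 2.4 (57.9 − 55.5) to 6.7 (46.7 − 40) points too high. Counting dropouts as failures moves the RR the other way, so in the last row the two readings of the plan give 1.35 and 1.51.

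**The case against.** - **The analysis plan may cover it.** Section 17a says complete plans will be finalised before data lock, and a condensed article need not list a method for every secondary outcome. Silence alone would be no finding. But section 20c is not silent: it states a condition on GEE, names a remedy, and directs that remedy elsewhere.
- **Dropout = failure may carry over.** Section 20a analyses the 6 to 18 month outcomes in the same way apart from the model, and the reason for the rule (dropouts are not taking medication) holds equally after month 6. This reading is open. On it, dropout would leave no missing values for long-run adherence or later HCV cure. Against it, section 20c ties the rule to the primary analyses, whereas section 20a says explicitly that its HIV-seroconversion rule applies to all PrEP adherence analyses. On either reading the rule gives no value to a missing infection test or risk-behaviour report.
- **Other provisions exist.** The missingness checks apply in all cases, and the MNAR sentence is not confined to the primary outcome. A reader might infer that the GEE outcomes are left with no protection at all; the text does not support that.
- **The harm outcomes are not 6 to 18 month outcomes.** A reader might also place infection and disinhibition in that GEE window. Section 20a follows them over the entire period, with a model given only by analogy.
- **The bias is small.** A reader might infer that a false harm signal is likely. The documents give neither a dropout rate nor a link between dropout and injecting risk, and the illustrated RR of 1.06 is about a third of a standard error. That objection stands.
- **Other remedies exist.** Weighted GEE, or GEE adjusted for the predictors of dropout, could serve. Making imputation the main analysis only after a positive missingness check would let the data choose the method, so that is not recommended.

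**Conclusion.** The mismatch is in the text and should be corrected. The stated MAR remedy goes to the co-primary outcomes, which are not described as GEE analyses and already count dropouts as failures. Long-run adherence and later HCV cure (6 to 18 months), and HCV infection, STI/HIV and risk behaviour (entire follow-up), have no stated MAR remedy; at most a conditional MNAR sensitivity analysis reaches them.

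The effect is confined to secondary outcomes. Its true size cannot be derived from the documents; the figures above rest on assumed dropout and assumed links between dropout and outcome. On those assumptions the RR shifts modestly and the absolute rates more. That matters mainly where 18-month rates are reported as such, or are carried into the cost-effectiveness model, which uses trial data.

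**What to change.** In section 20c, or in the analysis plan before data lock:

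1. Extend the multiple imputation analysis to all repeated-measures or GEE secondary outcomes, each over its own follow-up window. Pre-specify it, do not make it depend on a missingness test, and report it beside the available-case GEE.
2. Impute by arm, using site, venue, HCV stratum, and baseline and last observed risk behaviour. For a repeated outcome, its own earlier observed values belong in the model too.
3. State whether dropout = failure carries over to long-run PrEP adherence and later-initiated HCV cure. State that it does not apply to infection or risk-behaviour outcomes.
4. Keep the planned imputation analysis of the primary outcome.

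The cost is some extra analysis and slightly wider intervals. No new data are needed: site, venue and HCV antibody status are randomisation strata, and injection and sexual behaviour are collected at baseline and every 3 months (Table 3). Sample size, alpha and the co-primary tests stay as they are.

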#### Qualitative interview component

To be eligible to participate in the qualitative interview component, individuals must be an enrolled participant of the RCT in either intervention arm, must have completed the first 6 months of RCT follow-up, and must be able and willing to provide informed consent.

Following a purposeful maximum sampling strategy to optimize diversity (in terms of ages, sex and gender, level of adherence, etc.), participants are selected from both arms to ensure that most experiences are represented. Qualitative interview invitations are made to selected participants after the completion of the 6-month post-randomization follow-up visit. Interviews are scheduled according to participant availability. The interview guide addresses the following topics: (1) participant’s experience with the intervention (experience with the services offered in the experimental or the control group); (2) participant’s experience with PrEP, e.g., perception of their own risks and of the usefulness of taking PrEP, beliefs (and misbeliefs) and concerns about PrEP, management of the medication (including side effects); (3) contextual-level discussion of topics such as living conditions, other health problems such as mental health issues and intoxication/severity of substance use problem, and personal resources (work, housing, finances, education, peer norms, social support, health services access and utilization); (4) inquiry about any change in risk behavior and contextual factors involved.

Qualitative interviews are conducted by trained and bilingual (English and French or Spanish) interviewers in each city. They are digitally recorded for transcription. At the end of each interview, a report is produced by the interviewer. It includes notes on the interview conditions, i.e., all the elements that should be taken into consideration in the interpretation of the interview content (date, duration, location of the interview, state of the participant, etc.). The report will also include preliminary observations as well as suggested new avenues or hypotheses to explore in future interviews [70].

In accordance with the principle of data saturation [70, 71], we will continue sampling until new interviews no longer allow the construction or verification of important concepts related to the subject of study. Up to 100 participants (approximately 50 per city) will be interviewed.

Analyses of qualitative data will be carried out separately from the quantitative component as the qualitative component is intended to explore complementary research questions. However, quantitative results will also be examined with qualitative findings which inform the analyses and interpretation of both the quantitative and qualitative results [72].

We will use an iterative approach. Analyses will start from the beginning of interviews. Using an inductive approach, we will first identify the smallest units of meanings related to the study topic for each interview. Consistencies and variations in participants’ accounts will then be examined through constant comparative analysis, a method where the data are constantly revisited after initial coding until it is clear that no new themes are emerging [73]. Throughout these steps, we will bring out the meanings, social organization and strategies involved in PrEP use, and their relationships within the participants’ behaviors and life contexts. As the analyses will be carried out for each site, a final step of the analysis process will consist of contrasting and comparing both analyzed data sets in order to identify similarities and variations across sites in regard to the individual and structural factors that influence treatment adherence and behaviors.

The analysis process will involve the development of a mixed coding grid, based on both research questions and emerging themes in order to identify recurrent themes and conceptual categories. The software NVivo [74] will be used to help in this task. The categories identified with their properties will also be compared with theoretical concepts coming from the literature on medication adherence. This will ultimately allow us to compare our findings with the results of research conducted with other populations using PrEP and with people living with other conditions requiring prevention medication.

To ensure the validity of the analysis, we will employ a double coding procedure. Specifically, the coding of the same interviews by a second individual blind to the first coding will be performed on 25% of randomly selected interviews to evaluate the concordance of the analyses [75]. The researcher responsible for the qualitative component will supervise the entire analysis process, thus allowing an analysis from three points of view, which will enhance the validity of the conclusions. Results will be discussed in meetings with the research team.

Finally, integration of quantitative and qualitative results will be achieved using the joint displays technique and team discussions. Joint displays will provide visual means that will be used to stimulate discussions about the results and interpretation [76].

#### Cost and cost-effectiveness components

An assessment of healthcare services utilization and costs occurs in parallel to research procedures involving participants. Utilization of healthcare services delivered on site is documented in study records; healthcare services utilization outside of the intervention is collected directly from participants. Resources required to deliver the interventions in each arm will be estimated using established micro-costing methods [77]. Interviews will be conducted with site staff regarding time allocation and other resources utilized for delivering the interventions; site financial staff are asked to provide information regarding shared resources (“overhead”) with the exclusion of research-related costs.

Labor unit costs are estimated based on published labor rates in each location [78, 79]. Medication costs are estimated using Federal Supply Schedule costs for the US and published costs from Canada [80, 81]. Unit costs related to healthcare utilization outside of the trial and non-labor resources required to deliver the interventions will be estimated using local available data from Miami and Montreal (when available) and/or a systematic literature review. Using the guidelines from the Second Panel on Cost-Effectiveness in Health and Medicine, an annual discounting rate of 3% will be applied to costs and results will be reported in 2021 US dollars and Canadian dollars [82].

Results of the micro-costing analyses will be reported by arm as cost per participant enrolled on an intent-to-treat basis, as well as as-treated costs per participant to examine differences between each arm and across venues and sites. We will use a multivariable generalized linear model to predict mean costs for each healthcare service category by arm, controlling for baseline participant characteristics, including baseline service utilization. We will use the mean value of bootstrapped predictions to estimate the standard error of these healthcare costs, and a two-tailed *t*-test to estimate whether there are significant differences by study arm [83]. To capture both the long-term costs and benefits of the interventions for cost-effectiveness analysis, an extended time horizon — typically 10–25 years — is required. These include the individual benefits of HCV treatment and the public health benefits of reduced onward transmission of HIV and HCV due to PrEP and HCV treatment, respectively. Results will be generated from both the healthcare and societal perspectives. A dynamic computer simulation model (allowing HIV and HCV disease transmission between infected and susceptible segments of the population) will be used that will also capture the benefits derived from the prevention of 2nd- and 3rd-order HIV and HCV transmission [84]. We build on prior experience in both HIV [85, 86] and HCV [87–89] cost-effectiveness modeling, both alongside trials [90, 91] and in population-based settings [33, 86] to extend a previously validated dynamic compartmental HIV transmission model [85, 86, 91] to also capture the individual and public health benefits of HCV treatment. This model currently captures heterogeneity according to patient demographics, HIV risk group, and HIV disease progression [85, 92]. A subroutine capturing the progression of HCV among the infected and susceptible, informed by HCV model design considerations discussed in a recent review [93], and similar to our prior applications [87–89], will be implemented to capture the natural history of HCV. HCV transmission will also be integrated with HIV transmission in estimating the forces of infection of HIV and HCV associated with the integrated care intervention versus the standard of care.

Following past research on public health responses to HIV microepidemics in 6 US cities (including Miami), the dynamic compartmental HIV/HCV transmission model will be adapted, calibrated, and validated to match the epidemiological conditions of both Montreal and Miami [94–96]. A formal evidence synthesis will be conducted for each city, incorporating local surveillance reporting and other behavioral data if available [94]. Calibration and validation targets will then be chosen, and the model will be calibrated to match the epidemiological context of each city [95].

It is important to note that the interventions being assessed — PrEP to prevent HIV acquisition and DAA treatment to cure HCV — have both individual- and population-level impacts; the latter being the reduction in the onward transmission of HIV and HCV. As such, the population impact of these interventions will be dependent on local context — specifically, the sizes of the undiagnosed HIV and HCV populations, and the underlying availability of HIV, HCV, and harm reduction services in each city [96]. The incremental cost-effectiveness of the study intervention will therefore be assessed by city, with supporting sensitivity analyses to identify the key drivers of the differences in the cost-effectiveness of the intervention by city.

All cost-effectiveness analyses will be informed by recommendations of the Second Panel on Cost-effectiveness in Health and Medicine [82] and further adhere to best practices guidelines on model design [97], and reporting [98], and the calibration and validation [99] of dynamic infectious disease models [100]. Results will be reported as incremental cost-effectiveness ratios (ICER) comparing the two interventions within each city in US$/quality-adjusted life-years (QALY) and Cdn$/QALY at prevailing exchange rates. Both one-way and probabilistic sensitivity analyses [101] will be performed, focusing on demographic, venue, and site-level differences in the costs and effectiveness of the interventions. The healthcare resource analysis will consider different scenarios for achieving sustainability of the intervention depending on organizational and environmental considerations such as site volume, capacity, availability of services, and reimbursement rates for medications and services. We will follow established guidelines for budget impact analyses [102].

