### Sample size (14)

We will utilize an alpha of .025 to account for our two co-primary outcomes. Our sample will include 500 participants in the PrEP component and approximately 240 in the HCV component. We estimated power using a simulation program written for SAS 9.4. This program generated data with various constellations of treatment effects, site effects, venue effects, and interactions. A simple power analysis shows that with 500 participants and alpha = .025 that there is 90% power to uncover an absolute difference of approximately 15% (40% versus 55.5%, RR = 1.40) for main effects of the treatment arm (across site and venue). This power statement assumes that response rates are at the point of highest variance in the binomial distribution—i.e., variance decreases causing power to increase if the probabilities are actually further from .5 in either direction. We anticipate larger absolute differences but have kept the simple power high to account for the potentially complex interactions we might see. For example, with this sample size, the power for the primary (PrEP) outcome is about 86.8% when there are differences in site and venue of 13% and 16% respectively, and when power for the site and venue differences is greater than 80%. There is better than 80% power for an interaction effect (e.g., site by treatment) with a rate ratio [RR(site 1)/RR(site2)] of at least 1.37. Power for effects within a site or venue is around 90% for an absolute risk difference of .22 (40% versus 62%). Note that planned tests of differences (i.e., interactions) by the biological variable, sex, would need to have a rate ratio of 1.5 to have 80% power. For HCV outcomes, the sample size is expected to be smaller (*n* = 240); for the HCV primary hypothesis, there is 90% power to uncover an absolute difference of 21% (40% versus 63%, RR = 1.58), well within the range of what we expect for this intervention [63]. This is based on the extremely low rates of PrEP currently in our candidate venues and the relatively high rate of continuation (58%) in the open-label extension of the Bangkok Tenofovir Study where PrEP was provided without cost as is the case in the current protocol [63].

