## Assignment of interventions: allocation

### Sequence generation (16a)

Participants are randomized to one of two treatment groups in a 1:1 ratio. Randomization at the individual level uses a permuted-block randomization scheme to ensure relative balance across time; the block size is randomly permuted to prevent study staff from guessing the block size and inferring the condition to which the next participant will be assigned. Randomization tables have been generated by study statisticians separately for venues within site and by HCV antibody status.

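### The cost analysis names the mean of the bootstrapped predictions as the source of the standard error, which is the wrong quantity, and does not say what the t-test is applied to

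*Protocol article*

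**What the plan says.** The section Cost and cost-effectiveness components sets out three steps for comparing healthcare costs between arms.

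1. Model: "We will use a multivariable generalized linear model to predict mean costs for each healthcare service category by arm", with adjustment for baseline characteristics that include earlier service use.
2. Uncertainty: "We will use the mean value of bootstrapped predictions to estimate the standard error of these healthcare costs".
3. Test, in the same sentence and followed by a literature citation: "a two-tailed *t*-test to estimate whether there are significant differences by study arm [83".

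The section does not mention the standard deviation or the percentiles of the bootstrap distribution. It does not say which quantity the t-test compares. It gives no cost, spread, significance level or sample size for this comparison, and nothing elsewhere in the article adds to the description.

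**The concern.** A bootstrap yields a set of replicate estimates. Their mean is close to the estimate itself, here a mean cost. Their standard deviation is the bootstrap standard error. The sentence assigns the first quantity to the job of the second, so an analyst who follows the text literally would report a standard error as large as the mean cost and would find almost nothing significant.

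The t-test adds a second problem. Once the named standard error is unusable, the text does not lead to one definite test. Some of the ways to complete it are valid and others are far too liberal.

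At stake are the error bars and p-values for the arm difference in each healthcare service category. Healthcare utilization and cost-effectiveness form a stated objective (Objectives), and the cost-effectiveness results are among those prioritised for publication (Dissemination plans).

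**Working it through.** The article states no figure for this comparison, so there is nothing to reproduce. The check is of the logic, with simulation to show size.

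**Inputs from the article.** Total sample, from Sample size: "Our sample will include 500 participants in the PrEP component and approximately 240 in the HCV component". Allocation, from Sequence generation: "Participants are randomized to one of two treatment groups in a 1:1 ratio". Hence 500 / 2 = 250 per arm, assuming that all randomized participants enter the cost comparison.

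**Assumptions not in the article.** Gamma-distributed costs, log link, true mean about 1000 in both arms (no true difference), one baseline covariate, conditional coefficient of variation (CV) 1, 1.5 or 2, two-sided alpha 0.05, 200 bootstrap resamples of participants within arm with the model refitted each time, and 400 simulated trials per CV.

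**Formulas.** Let d be the adjusted arm difference in mean predicted cost, and d*(b) its value in resample b.
- Mean of bootstrapped predictions: the average over b of the predicted arm mean.
- Bootstrap standard error of d: the standard deviation of d*(b) over b.

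**Step 1: what the mean of the predictions measures.**

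| CV | Mean of bootstrapped predictions (two arms) | Average SD of d*(b) | True sampling SD of d |
|---|---|---|---|
| 1 | 1003.1, 1004.6 | 89.6 | 92.6 |
| 1.5 | 998.8, 998.8 | 133.1 | 133.4 |
| 2 | 997.9, 997.7 | 177.3 | 173.1 |

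The mean of the predictions recovers the mean cost and does not respond to the CV. The standard deviation of the replicates tracks the true sampling spread. Taking about 1000 as the standard error of the difference would overstate it by a factor of 1000 / 177.3 = 5.6 to 1000 / 89.6 = 11.2 in these settings.

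**Step 2: three ways to complete the t-test.** Type I error at nominal 0.05:

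| What is tested | CV 1 | CV 1.5 | CV 2 |
|---|---|---|---|
| (a) d divided by SD of d*(b) | 0.060 | 0.050 | 0.037 |
| (b) participants' predicted costs, arm against arm | 0.443 | 0.647 | 0.647 |
| (c) bootstrap replicates, arm against arm | 0.895 | 0.892 | 0.858 |

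The simulation error of a rate of 0.05 is √(0.05 × 0.95 / 400) = 0.011, so (a) is nominal within noise.

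**Step 3: why (b) and (c) fail.** In (b), fitted values carry no residual cost variation. In the limit of no covariates, every participant in an arm has the same prediction, and the test's standard error is zero. A second set of assumptions (gamma shape 0.6, two covariates with log-scale effects 0.2, 0.35 and 0.6, 600 trials each) shows the same pattern. The test's mean standard error was 64, 120 and 251, against true values of 353, 397 and 473. The ratios are 64/353 = 0.18, 120/397 = 0.30 and 251/473 = 0.53, and type I error was 0.725, 0.558 and 0.298.

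In (c), the test divides the spread by the square root of the number of resamples. With 200 resamples its standard error is about 1/√200 = 1/14.1 of the right one. The critical value of 1.97 then acts like 1.97 / 14.1 = 0.14 on the proper scale, which a null statistic exceeds in about 89% of trials. This agrees with the simulated 0.86 to 0.90, and the rate would rise further with more resamples.

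**The case against.** The strongest reply is that the sentence is compressed wording for a standard procedure: bootstrap the adjusted arm means, report their average, take the standard error from their spread, and divide the arm difference by it. The preceding sentence speaks of mean costs by arm, which fits this reading better than a test on individual fitted values. A reference is cited for the step, and the blinding section says that complete analysis plans will be finalized before data lock. Under this reading the test is valid, as row (a) shows.

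Much of this stands. A reader might infer that the trial's cost test will certainly be invalid, or that its false-positive rate will be 30% or more. The article supports neither: it nowhere says that the test will be run on fitted values or on replicates. A reader might also conclude that the t-test has to go. That does not follow, because a two-tailed t-test on the adjusted difference over its bootstrap standard error keeps its level at 250 per arm. Finally, a reader might infer that the incremental cost-effectiveness ratios are compromised. The article derives those from a dynamic transmission model by city, with its own sensitivity analyses, and does not say that this p-value or standard error enters them.

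What does not stand is that condensing explains the sentence away. Condensing accounts for missing detail, whereas this sentence supplies a detail and names the wrong quantity. A cited source or a later plan may describe a sound method, but an analyst would have to depart from this text to apply it.

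**Conclusion.** The point holds in a limited form. As written, the rule for the standard error is wrong, and this follows from the definition of a bootstrap standard error without any distributional assumption. The object of the t-test is not fixed, and the choice matters: about 0.04 to 0.06 type I error for the sound version, against about 0.3 to 0.9 for the two unsound ones. Those rates are illustrative. They rest on assumed gamma costs, covariate strengths, an alpha of 0.05 and 250 per arm, and they are not estimates of what this trial will do.

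The scope is the between-arm comparison of healthcare costs by service category. The point estimates of cost and the two co-primary endpoints are not touched.

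**What to change.** Replace the sentence on the standard error and the test with a statement of three things:

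- The generalized linear model is refitted in each bootstrap resample of participants, and the adjusted between-arm difference in mean predicted cost is computed each time.
- The standard error is the standard deviation of those bootstrapped differences; alternatively, the interval is given by their percentile or BCa limits.
- The two-sided test uses the adjusted difference and that standard error. It is not run on participants' predicted values, nor on replicates treated as independent observations.

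The two-tailed t-test can remain in this form. The bootstrap is already planned, so the change costs only wording and needs no new data.
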